#### Vitamin D

In the questionnaire days travelled to a warmer climate in winter or spring and number of sun beds will be asked. The month of blood collections will be noted to link this to vitamin D content.

The use of multivitamin pills and their dosage will be recorded and the amount of vitamin D/placebo pills missed (compliance) will be noted based on self-report and by pill counter at the measurements session from returned bottles.

Adverse events like hypercalciuria (≥2.27 mmol/mmol calcium/creatinine) and hypercalcaemia will be checked for locally at all measurements (at 24–28 weeks >9.0 mg/dl | 2.25 mmol/l; and at 35–37 weeks > 9.7 mg/dl | 2.43 mmol/l).

#### Psychosocial factors

Based on the Health Action Process Approach (HAPA) model
[66] we will assess perceived importance, outcome expectancy, self-efficacy and intention related to weight control, physical activity and nutrition. These factors have been shown to be important predictors in healthy pregnant women or in women with (previous) GDM
[67-69] and captured with single validated items that have been used in previous studies. The stage of change questions for physical activity and nutrition behaviour are adapted from Te Wai O Rona: Diabetes Prevention Strategy
[19], itself adapted from Prochaska
[70]. Mental Health (stress, depression, anxiety) has been shown to affect birth weight and gestational age
[71]. Therefore we chose to measure mental health with the widely-used WHO well being index
[72] and pregnancy specific worries with the Cambridge worry scale
[73]. To measure health related quality of life the EuroQol (EQ 5D) will be used
[74].

#### Other

Social demographics, like household composition, marital status, ethnicity (maternal, paternal and of grandparents), education, employment, occupation, shift work, parity, age and paternal information will be obtained.

In the questionnaire information on pre-existing conditions is included: family history of diabetes, previous GDM diagnosis, IGT, hypertension and PCOS. Past/current obstetric history and medication / vitamin use is assessed also.

Co-morbidities, sick leave and complications during pregnancy or delivery will be assessed. Obstetrical and perinatal complications will be registered, such as spontaneous or induced abortion before 22 weeks, intra-uterine death at or after 22 weeks gestation, hypertensive diseases, preeclampsia, pre-term delivery (<37 weeks), need for labour induction or augmentation, assisted vaginal delivery, shoulder dystocia, maternal haemorrhage and caesarean section. Also adverse events for the neonate, such as hypoglycaemia, hyperbilirubinaemia (with or without therapy), respiratory distress, congenital malformation, admission to the neonatal (intensive) care unit, stillbirth, early or late neonatal death will be registered.

### Primary outcome measures

For assessing intervention effects, the primary outcomes are maternal weight gain, fasting glucose levels and insulin sensitivity. Maternal weight gain will be defined as the weight change from baseline measurement to the last measurement at 35–37 weeks of gestation. Insulin sensitivity will be derived from homeostasis model assessment (HOMA)
[75].

#### Economic evaluation

This study will include an economic evaluation to assess the cost-effectiveness of the intervention.

All direct costs, medical and nonmedical, and indirect cost, morbidity and mortality, will be registered.

Regarding economic evaluation of prevention strategies, the cost-effectiveness analysis will be carried out from a societal perspective. Moreover, we will assume the following general principles when performing the analysis: 1) intention to treat 2) the time horizon will be extended to 10 weeks postpartum to register all cost and benefits, and 3) an assessment of uncertainty in final outputs will be applied. In this case, univariate and multivariate analyses of strategies and scenarios (including discounting rates) will be undertaken. Finally a multivariate analysis of possible scenarios related to epidemiological variations, costs and benefits will be performed. Furthermore, cost-effectiveness, and cost utility mean ratios of each intervention will be calculated and compared. Incremental cost-effectiveness ratios (Δ Costs /Δ Effectiveness) and net health benefits (according to willingness to pay) of each intervention will be calculated. Additionally, the degrees of dominance of competing strategies will be analyzed by using the efficiency frontier graphs. Univariate (ie. tornado graphs- for detecting the most sensitive parameters) and multivariate sensitivity analyses (ie. confidential intervals and nonparametric-bootstrapping) will be performed. Moreover, a budgeting impact of the introduction of the most efficient strategies will be carried out aiming to highlight the feasibility of introducing those strategies. Finally, data from this prospective study will enable us to perform a decision modeling for health economic evaluation of the introduction of the different strategies in Europe to prevent GDM in time horizons of 3 and 5 years and applying a discounting rate for costs and benefits (ie. 3.5%). This model will allow investigators to estimate cost-effectiveness of the interventions in simulated cohort studies in each of the sites.

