[82]. The DALI study will aim to close this gap in knowledge and will evaluate the potential effectiveness of vitamin D supplementation on the risk of developing GDM, something which is needed especially for certain population groups, but also for the countries and the rising incidence of GDM and T2D
[83]. DALI will also be the first study to assess whether vitamin D supplementation will provide additional benefits on the capability to reduce the risk of GDM beyond lifestyle alone.

Biobanking on a European level has been recognised as one of the major resources promoting biomedical research. This will allow future comparison of the metabolic phenotype and genotype of responders and non-responders after consideration of the psychological and situational characteristics of participating women. The robust trial monitoring and methods to maintain fidelity of the trial will maximise the confidence that any difference in response is due to differences between participants rather than differences in the way the trial was delivered. Maintaining fidelity is something of particular importance when intervening across 9 countries with their own languages, cultures and health systems.

The information obtained from this trial can be used to inform and develop public health policies Europe-wide in pregnancy and pregnancy related prevention of GDM. The overall aim of the DALI study is to identify the best available measures to prevent GDM in an ongoing pregnancy, to provide cost-benefit calculation of GDM prevention for health care systems, and to establish a pan-European cohort of mother-offspring pairs for future analyses with a central biobank and database.

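### The economic plan compares average cost-effectiveness and cost-utility ratios between arms, a comparison that can contradict its own net-health-benefit yardstick in either direction

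*Protocol article*

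**What the plan says.** The Economic evaluation section of the protocol article commits to this: "Furthermore, cost-effectiveness, and cost utility mean ratios of each intervention will be calculated and compared".

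The sentence after it introduces the incremental measures as something separate: "Incremental cost-effectiveness ratios (Δ Costs /Δ Effectiveness) and net health benefits (according to willingness to pay) of each intervention will be calculated". A frontier analysis follows: "the degrees of dominance of competing strategies will be analyzed by using the efficiency frontier graphs". Nonparametric bootstrapping is listed among the sensitivity analyses.

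The section then plans that "a budgeting impact of the introduction of the most efficient strategies will be carried out aiming to highlight the feasibility of introducing those strategies". It does not say which measure identifies those strategies.

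Three further statements set the scale of the ratios:
- **Perspective:** "the cost-effectiveness analysis will be carried out from a societal perspective", so background pregnancy and delivery costs enter every arm's total.
- **Horizon:** "the time horizon will be extended to 10 weeks postpartum to register all cost and benefits".
- **Utilities:** under Psychosocial factors, "To measure health related quality of life the EuroQol (EQ 5D) will be used".

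The Discussion names the economic answer as part of the overall aim: "to provide cost-benefit calculation of GDM prevention for health care systems".

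**The concern.** Because incremental ratios are defined separately as a difference in cost over a difference in effect, the mean ratios of each intervention are most naturally read as average cost over average effect within an arm. The plan says they will be compared, not merely reported. The Randomisation section counts control among the eight arms, so usual care would be part of that comparison.

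An average ratio mixes the intervention's own cost and effect with the cost and health that every pregnant woman accrues anyway. Over a horizon that ends 10 weeks after birth, and from a societal perspective, that background is likely to dominate both numerator and denominator. A comparison of such ratios need not agree with net health benefit, which appears one sentence later. If a reader took the order of the average ratios as an order of value, the trial's message to health care systems could be wrong in either direction.

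**Working it through.** **Inputs.** The documents give no costs, QALYs or willingness to pay, so there is no planned figure to reproduce. The planned measures come from the Economic evaluation section. Every number below is an assumption chosen for illustration.

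**Algebra.** Let usual care have mean cost C0 and mean effect E0 > 0, and let an intervention have C0 + dC and E0 + dE with dE > 0.

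1. The average ratio favours the intervention when (C0 + dC)/(E0 + dE) < C0/E0.
2. Cross-multiplying gives dC × E0 < dE × C0, that is, dC/dE < C0/E0.
3. With willingness to pay λ, incremental net health benefit is dE − dC/λ. It is positive when dC/dE < λ.

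Both are tests of the incremental ratio dC/dE (the ICER). The first uses C0/E0 as its threshold and the second uses λ. They conflict in two cases:
- C0/E0 < ICER < λ: a cost-effective intervention ranks below usual care.
- λ < ICER < C0/E0: an intervention that is not cost-effective ranks above usual care.

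The same holds between two active arms, with the arm of lower effect in the place of usual care.

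**Example 1: cost-effective, but ranked below usual care.** C0 = EUR 4,000, E0 = 0.53 QALY, dC = 400, dE = 0.03, λ = 30,000 per QALY.
- Usual care: 4,000/0.53 = 7,547 per QALY.
- Intervention: 4,400/0.56 = 7,857 per QALY, which is worse.
- ICER: 400/0.03 = 13,333, below λ.
- Net monetary benefit: 0.03 × 30,000 − 400 = +500.

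**Where example 1 stops conflicting.** The measures agree once C0/0.53 exceeds 13,333, that is, C0 above 13,333 × 0.53 ≈ EUR 7,070. At C0 = 10,000 the ratios are 10,400/0.56 = 18,571 for the intervention and 10,000/0.53 = 18,868 for usual care, so both measures favour the intervention.

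**Example 2: a different horizon.** Assume entry at 20 weeks and delivery at 40. The horizon is then 20 + 10 = 30 weeks, or 30/52.18 = 0.575 year. At utility 0.8, E0 = 0.460 QALY.

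| C0 | dC | dE | ICER | Usual-care ratio | Intervention ratio | Net health benefit |
|---|---|---|---|---|---|---|
| 5,000 | 300 | 0.02 | 15,000 | 10,871 | 11,043 | 0.02 − 300/20,000 = +0.005 |
| 15,000 | 500 | 0.02 | 25,000 | 32,612 | 32,295 | 0.02 − 500/20,000 = −0.005 |

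Both rows use λ = 20,000. The first ranks a cost-effective intervention below usual care. The second ranks one that is not cost-effective above it.

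**Range of the implied threshold.** Over 0.575 year, C0/E0 runs from 2,000/(0.9 × 0.575) ≈ 3,900 to 20,000/(0.7 × 0.575) ≈ 49,700 per QALY, for background costs of 2,000 to 20,000 and utilities of 0.7 to 0.9. None of these inputs describes the intervention.

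**The case against.** The strongest reply is that the protocol adopts no such rule. It says average ratios will be calculated and compared, never that arms are ranked or chosen on them. The same paragraph plans ICERs, net health benefit, an efficiency frontier and bootstrapping. The frontier is the tool described for competing strategies, and the budget-impact sentence comes after it, so reading the most efficient strategies as those on the frontier is at least as natural as reading them as those with the lowest average ratio. Which summary governs is a detail that an article may leave to an analysis plan.

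Much of this stands. A reader might infer that the average ratio decides the economic question, or that it feeds the budget-impact step. The text says neither. A reader might also infer that the average ratio ignores the intervention's effect. It does not: dC/dE enters, but against the wrong threshold. Nor does it help to note that, if nothing works, chance orders the arms. That is equally true of net benefit.

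Two further limits apply. The numerical examples depend on assumed costs, and the first one resolves above about EUR 7,070. The effect measure for the cost-effectiveness ratios is not specified, so the QALY figures speak only to cost-utility. The algebra covers any effect measure for which E0 is positive and more is better.

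What does not fall is the comparison itself. It is stated in the text, as a comparison, and separately from the incremental measures. The point is therefore more than a missing order of precedence.

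**Conclusion.** The concern holds in a limited form. The protocol plans a between-arm comparison of average ratios whose implicit threshold is the background cost per unit of effect, and this can contradict the plan's own net health benefit in either direction. Whether it would do so in this trial, and in which direction, cannot be known from the documents, because it depends on where the ICER lies relative to C0/E0 and the willingness to pay.

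The weight is minor to moderate. The flaw is confined to the economic evaluation, does not touch the primary outcomes, and sits beside valid methods that are already planned. The conclusion rests on reading the mean ratios as average cost over average effect per arm, which the separate sentence on incremental ratios supports.

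**What to change.** In the Economic evaluation section, delete the between-arm comparison of mean ratios, or keep the ratios and label them descriptive only. State that strategies are compared by ICERs along the efficiency frontier and by incremental net health benefit, with bootstrap uncertainty. State also that the same measures decide which strategies count as most efficient for the budget-impact step.

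The cost is one sentence removed or relabelled and one reworded, since every tool named is already planned. The downside is that mean ratios are no longer available as a ranking.

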### Database

All trial subject data is entered into a web-based electronic database using the Microsoft.Net development environment that is accessible from any web-enabled computer, tablet or cell phone. The database is housed on an SQL server that employs a certificate and is housed in a physically-secure location. Pages are in English and employ drop-down menus, pick-lists and text boxes, and are encrypted with Standard SSL level encryption. Operator entry is password protected. No personal identifiers for study subjects are housed within the database; rather they are cross-referenced to a unique study number, the first two digits of which indicate the geographic clinical site. The security and confidentiality standards of the database are compliant with those required under HIPAA privacy rules established by the National Institutes of Health, U.S.A., and the recommendations of EuroSOCAP. Back-up copies of the entire database are made daily. A Data Management Board has been created to oversee the integrity of data and to determine its academic usage.

### Process evaluation

Process evaluation
[76] will be used to gain insight into the response rate of the target population (reach), behaviour changes, implementation, fidelity (the extent to which the intervention was delivered as planned), delivered dose (the amount of the intervention actually delivered) and participants perceptions (satisfaction). For this the recruitment database, counselling logs on the PDA, evaluation questionnaire and the MITI 3.1.1 code
[25] will be used.

### Data analysis

Multilevel analyses will be performed, to take the clustering effect into account, since the success of treatment can be dependent on the skills of the provider as well as specific characteristics of a treatment centre. Longitudinal, linear regression analyses will be performed to assess intervention effects. In these analyses, the correlation between multiple measurements within one individual is taken into account. The regression coefficient reflects the average difference in the outcome variable between conditions. Possible confounders will be entered into the regression analyses. Confounding will be defined as a change in the regression coefficient of 10% or more. Possible effect modification will be studied as well, defined as a significant (p <0.10) interaction-term between group allocation and the variable concerned. Data will be analysed according to the intention-to-treat principle.

Interactions between interventions will be assessed, and when not present, groups will be combined.

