#### Sample size and power calculation

The primary outcomes of the study are gestational weight gain, fasting glucose and insulin sensitivity in late pregnancy. The numbers needed in each arm (80% power, 5% significance, two tailed alpha) were calculated assuming a 20% drop out. To detect a weight gain difference of 4 kg (mean of 11 kg and standard deviation (SD) of 6.5 kg) we would need 80 women in each arm. To measure a fasting glucose difference of 0.3 mmol/l (mean of 5.0 mmol/l and a SD of 0.5 mmol/l) we would need 85 women in each arm. To find a difference 0.44 for the HOMA-IR (mean of 2.2 and a SD of 0.8) we would need 101 women in each arm. Lesser numbers are required when using the factorial design, combining cells for comparisons. The trial will be conducted in nine European countries (ten study centres) and in each centre 88 women will be recruited (total n = 880) before 20 weeks of pregnancy and randomly assigned to one of the eight arms pre-stratified for centre and 2x2 trial (lifestyle 2x2 or vitamin D/placebo 2x2).

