#### Oral glucose tolerance test (OGTT)

At baseline, 24–28 and 35–37 weeks an OGTT is performed. After an overnight fast of 10 hours, a fasting blood sample is collected, immediately followed by the administration of 250 ml 75 g glucose drink (within a period of 5 minutes). Further blood collections take place at the time points 60 and 120 minutes in which only glucose and insulin will be assessed. At some sites blood will also be collected at 30 and 90 minutes. Participants are instructed not to walk, eat or drink extensively during this test. For clinical practice use and inclusion in the study glucose will be measured in the blood samples at 0, 60 and 120 minutes in the local laboratories at baseline and 24–28 weeks of gestation, some centers will locally analyze the 35–37 weeks sample as well.

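### Covariates are to be chosen by a 10% change in the treatment coefficient, which leaves the primary model of a randomised trial open until outcomes are seen

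*Protocol article*

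**What the plan says.** Data analysis describes the effect model in a few sentences. The structure is multilevel ("Multilevel analyses will be performed, to take the clustering effect into account") and longitudinal ("Longitudinal, linear regression analyses will be performed to assess intervention effects"), and "the correlation between multiple measurements within one individual is taken into account". Covariates are governed by two sentences: "Possible confounders will be entered into the regression analyses", followed by "Confounding will be defined as a change in the regression coefficient of 10% or more". No covariate is named as fixed in advance, and the candidates are not listed.

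Three other places bear on the point:

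- Primary outcome measures: "Maternal weight gain will be defined as the weight change from baseline measurement to the last measurement at 35–37 weeks of gestation". Fasting glucose and HOMA-based insulin sensitivity are not defined as changes.
- Oral glucose tolerance test: "At baseline, 24–28 and 35–37 weeks an OGTT is performed", so baseline glucose and insulin are available.
- Sample size and power calculation, and Randomisation: allocation is stratified by centre and by 2x2 trial.

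**The concern.** A change-in-estimate rule belongs to observational work, where a covariate that moves the exposure coefficient may be a source of bias. After randomisation, baseline differences between arms are chance, and the main reason to adjust is precision. The rule ignores how strongly a covariate predicts the outcome and looks only at how far it shifts the treatment estimate in the data at hand.

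The threshold is also relative to that estimate. Near a null effect almost any prognostic covariate passes, because 10% of a small number is tiny. With a large effect a strongly prognostic covariate can fail. The same variable can therefore be in the model for one primary outcome or factorial contrast and out of it for another. With three primary outcomes, several contrasts and an unlisted set of candidates, the model that produces the primary result is not known until the outcomes have been analysed.

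This is a stated method and not a detail left to a later document: an analysis plan faithful to the text would carry the rule forward.

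**Working it through.** The article gives no figure for how the rule behaves, so there is none to reproduce. The check asks how often the rule drops a prognostic baseline covariate and what that does to the inference.

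**Inputs from the article**

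- Planned effects and SDs (Sample size and power calculation), as standardised effects d: weight gain 4/6.5 = 0.615; fasting glucose 0.3/0.5 = 0.60; HOMA-IR 0.44/0.8 = 0.55. A 2 kg effect is 2/6.5 = 0.308.
- Completers: 110 per arm less 20% dropout = 88. Two arms against two within one 2x2 trial: 2 × 88 = 176 per group.

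**Assumption**

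- Correlation ρ between baseline covariate and outcome: not in the article. 0.5 is used for illustration, with a range of 0.2 to 0.8.

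**Share of trials in which the covariate is dropped**

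In standardised units, adjustment changes the coefficient by about ρ times the chance baseline difference, whose SD is √(2/n). The covariate is dropped when this change is below 0.1·d. Hence

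P(dropped) ≈ 2Φ(0.1·d·√(n/2)/ρ) − 1.

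- 2 kg, n = 88, ρ = 0.5: 0.1 × 0.308 × 6.633/0.5 = 0.41, giving 32%.
- 4 kg, n = 88, ρ = 0.5: 0.1 × 0.615 × 6.633/0.5 = 0.82, giving 59%.
- d = 0.60, n = 176, ρ = 0.5: 0.1 × 0.60 × 9.381/0.5 = 1.13, giving 74%.

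Simulated two-arm trials agree: 33% dropped at 2 kg, 58% at 4 kg, and 74% for d = 0.60 with combined cells. The formula puts the true effect in place of the observed one, so it does not apply at d = 0. There, simulation gives about 10%.

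Simulated share dropped at d = 0.60, by assumed ρ:

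| ρ | 88 v 88 | 176 v 176 |
|---|---|---|
| 0.2 | 91% | 98% |
| 0.3 | 79% | 92% |
| 0.5 | 58% | 74% |
| 0.6 | 50% | 65% |
| 0.7 | 44% | 58% |
| 0.8 | 38% | 52% |

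At half the planned effect (d = 0.30) and ρ = 0.5 the shares are 32% and 42%.

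**Effect on inference (one baseline candidate, 88 per arm)**

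| Setting | Fixed adjustment | 10% rule |
|---|---|---|
| d = 0.60, ρ = 0.5: true SD / mean SE | 0.132 / 0.131 | 0.136 / 0.142 |
| d = 0.60, ρ = 0.5: 95% CI coverage | 94.7% | 95.7% |
| d = 0.60, ρ = 0.5: power | 99.5% | 99.4% |
| d = 0.30, ρ = 0.5: power | 63.0% | 59.4% |
| d = 0.30, ρ = 0.7: power | 78.5% | 73.3% |
| d = 0, ρ = 0.5: type I error | 5.0% | 4.3% |

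Under the rule at d = 0.60 the mean standard error exceeds the true SD by 0.142/0.136 = 1.04 at ρ = 0.5, and by 0.127/0.112 = 1.13 at ρ = 0.7. With nine pure-noise candidates added at ρ = 0.5 the ratio is 0.1424/0.1336 = 1.07. About 5% is a fair summary at ρ = 0.5. With combined cells at d = 0.30, power is 89.6% v 87.9% (ρ = 0.5) and 97.6% v 95.6% (ρ = 0.7).

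With ten candidates chosen by forward selection, type I error was 4.5% to 5.7%. The 5.7% arose only when all ten were pure noise.

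**The case against.** Three stronger readings are tempting, and the article does not support them.

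**The baseline outcome value is discarded in most trials with a real effect.** The article never says that the baseline outcome is one of the candidates. Weight gain is already a change from baseline, and the longitudinal model may carry baseline glucose and HOMA as repeated measurements. Centre sits in the multilevel structure and is not stated to depend on the rule. Even for a covariate that is subject to the rule, *most* fails at 2 kg (33% dropped at ρ = 0.5). At the planned effect it fails for single arms once ρ exceeds about 0.6. What stands against this objection is that nothing guarantees inclusion: a change score is not the same as adjustment for baseline, and two of the three primary outcomes are not defined as changes.

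**The standard errors are wrong and false positives follow.** The unadjusted standard error is valid in a randomised comparison. After selection the error is on the large side, so the inference is mostly conservative.

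**The rule costs ten or more points of power.** A simulation with eight independent covariates and a 2 kg effect does give 72% under the rule against 83% with all eight fixed. But one covariate at r = 0.5 and seven at r = 0.2 explain 0.25 + 7 × 0.04 = 53% of the variance, which nothing in the article supports, and the effect is half the planned one. In the same scenario a fixed model with baseline and three further covariates reaches 71%, no better than the rule.

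It is also fair to say that at the planned effects power is hardly touched.

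**Conclusion.** The point holds as a flaw of method with a modest, conservative numerical cost. The rule is stated, it suits observational data, and it makes the primary model depend on the outcomes and vary between outcomes and contrasts. The room this leaves for choosing among unlisted candidates is the main reason to change it; that part is not quantified here.

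The figures apply to any baseline covariate that is put through the rule and rest on an assumed correlation. For single arms at the planned effect, the share dropped runs from 91% to 38% as the correlation goes from 0.2 to 0.8. The inflation of the standard error after selection grows with the correlation, to about 13% at 0.7 and 21% at 0.8. The loss of 3 to 5 points of power belongs to half the planned effect with 88 per arm and correlations of 0.5 to 0.7; with combined cells it is about 2 points. No material inflation of the type I error was found.

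**What to change.** Replace the two sentences on confounding with a covariate set fixed in advance for each primary outcome and entered whatever it does to the treatment coefficient:

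- the baseline value of that outcome: baseline weight for weight gain, baseline fasting glucose, baseline HOMA;
- the stratification factors: centre (which may stay as a level of the multilevel model) and 2x2 trial, where an analysis uses both trials;
- gestational age at the baseline visit.

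Use no covariate measured after randomisation, which rules out gestational age at the outcome visit. If the longitudinal model is meant to handle baseline as a repeated measurement, say so explicitly. Any change-in-estimate analysis should be labelled exploratory.

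The cost is wording only. Table 1 already lists weight, fasting glucose and insulin at baseline, and an early dating scan is required where baseline falls after 16 weeks. The change should be made before outcome data are examined.
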